## **3. INVESTIGATIONAL TRIAL DESIGN**

### **3.1 Study Endpoint(s)**

The primary endpoint will be lesions cure rate and cosmetic outcome by treatment regime 1 compared to lesions cure rate by treatment regime 2, assessed 36 months after PDT. The number of lesion in need of a re-treatment 3 months following the first treatment session in regime 1 will be reported. Clinical suspected recurrences are confirmed by histology. Lesion response rate is defined as number of lesions in complete response at 12 and 36 months of follow-up. We will report on adverse events occurring in relation to both treatment regimes from start of treatment to 3 months following last treatment. We will report on lesion recurrences among lesions treated with either regime 12 and 36 months after PDT. Cosmetic outcome will be determined by clinical assessment (visual inspection and palpation) 12 and 36 months after treatment. The results will be recorded on a 4-point ordinal scale as either excellent (absence of any stigmata other than scar formation after diagnostic punch biopsy), good (slight presence of fibrosis, atrophy or change of pigmentation), fair (moderate presence of fibrosis, atrophy or change of pigmentation) or poor (marked presence of fibrosis, atrophy or change of pigmentation).

The secondary endpoint will be to investigate relationship between clinical and pathological tumour characteristics and tumour recurrences rates, tumour thickness, histopathological BCC subtypes and immunohistochemical markers. Recurrence rate defined both as "raw" (total number of recurrences divided by the total number of tumours treated) and "strict recurrence rate" (total number of patients with recurrence divided by number of lesions observed for at least 36 month) will be reported.

Recurrence rate in relation to BCC subgroup analyses including clinical (superficial or nodular tumour), tumour size and histological characteristics will also be reported. BCC will on the basis of histological growth pattern be divided into two main types (aggressive or non-aggressive type). Tumours will additionally be studied with various immunohistochemical markers for expression of cell proliferation, invasiveness, vascularisation and growth factors.

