**Procedure** Lesion mapping will take place before treatment and at the preset follow-up visits by recording the number and location of the lesions in the CRF. Registration of the lesion clinical extent, location, thickness and subtype will be done at baseline and marked on a form and/ or photographed for later identification. In order to facilitate access of the Metvix® cream and light to all parts of the lesion, the surface of BCC lesions with 5 mm of the surrounding tissue of normal appearance should be prepared using a small dermal curette. The curettage should be performed by scraping in a checked pattern for optimal removal of scales and crusts, and to roughen the surface of the lesion. Thicker lesions require debulking. Metvix® cream will then be applied in a 1.0 mm thick layer to the whole treatment field and then covered using a dressing to avoid any ambient light exposure. Metvix® is applied for 3 hours before the dressing and remnants of cream are removed. Anaesthesia using subcutaneous infiltration anaesthesia without adrenaline will be given individually at the discretion of the investigator. The treatment area is then illuminated using Aktelite CL 128

(Photocure ASA) as a light source; peak wavelength around 631 nm (redlight) and light dose 37 J/cm^2 and exposure time 7-9 minutes. After light treatment each lesion will be randomized to one or two possible treatment regimes; a single MAL-PDT treatment session with re-treatment if there is a non-complete response after 3 months (regimen 1), or two treatment sessions separated by one week (regimen 2).

Two independent pathologists will examine the HES stained diagnostic punch biopsies. Tumour thickness and subtype will be recorded. Various immunohistochemical stains will be used to evaluate their utility for enhanced detection of residual tumours.

**Endpoints** The primary endpoint will be lesions response rate and cosmetic outcome determined by clinical assessment (visual inspection and palpation) 1 and 3 years after Metvix® PDT treatment. Clinically suspected recurrences will be examined by histology. We will report the number of lesion in need of a re-treatment 3 months following the first treatment session in regime 1. Further, report on number and time of lesion to relapse by either regime, 1 or 3 years after PDT and report on adverse events in a period of up to 3 months following last treatment session.

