## **1.2 Benefits and Risks**

Metvix® PDT is an approved and marked treatment modality for patients with pre-malignant disease and BCC.

General benefits of topical Metvix® PDT include:

- Non-invasive treatment available on an outpatient basis
- Several separate lesions can be treated simultaneously
- The same lesion(s) can be treated repeatedly with success
- Excellent cosmetic results
- No known toxicity or interaction with other medication
- Lesion selective, leaving the surrounding tissue intact
- No skin photosensitization after 24 hours
- Only minor, manageable local side effects related to treatment site

Study benefits include the following:

If the effect of the new, alternative and simpler treatment regime proves as effective as the standard approved regime MAL-PDT will be an even more attractive therapy alternative for low-risk BCC. The treatment will be easier to manage with improved cost-effectiveness as well as reduced discomfort and fewer side effects for the patients.

The risks attributed to Metvix® PDT are few and related mainly to transient discomfort and pain during and shortly after illumination. Inflammation following tumour destruction may give local, transient erythema and oedema. Treatment of large lesions may cause severe erythema, followed by ulceration. These side effects normally last for a few days, in rare occasions up to a week after treatment.

Standard Metvix® PDT in BCC is today given as two treatment sessions separated by one week. Patients with non-complete response after one PDT session in treatment regime 1 are offered an additional PDT at the 3-month control. The possible delay of the second session of BCC treatment is acceptable, as BCC grows very slowly

Patients with non-complete response after either PDT treatment regimes at the control visit 3 months after the latest treatment session are withdrawn from the study. They are then offered standard BCC treatment at the discretion of the dermatologist. Patients will receive detailed oral and written information about the risks of side effects. If the patients find the side effects unacceptable, they are free to withdraw from the study at any time and without any further explanation.

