### 5.6.2 Safety follow-up

In case of any adverse event patients should take contact with their G.P. or the local hospital for further consultation. Adverse event will be recorded in the CRF at the follow-up visits if related to treatment, according to the investigator

Follow-up:

| Treatment regime/ lesions                                                              | Follow-up/ months after treatment  |
|-----------------------------------------------------------------------------------------------|-------------------------------------------|
| Regime 1/ all lesions                                                                         | 3 months after 1 treatment session        |
| Regime 1/ lesions with non-complete response 3 months after first session with a re-treatment | 3 months after 2 treatment session        |
| Regime 1/ all lesions in complete response                                                    | 12 months after 1 or 2 treatment sessions |
| Regime 1/ all lesions in complete response                                                    | 36 months after 1 or 2 treatment sessions |
| Regime 2/ all lesions                                                                         | 3 months after 2 treatment session        |
| Regime 2/ all lesions in complete response                                                    | 12 months after 2 treatment sessions      |
| Regime 2/ all lesions in complete response                                                    | 36 months after 2 treatment sessions      |

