### **Per-protocol (PP) efficacy population**

This population will consist of all treated BCC-lesions, except lesions considered not evaluable due to major deviations from the protocol. Major deviations may include: inclusion criteria not respected, non-available efficacy assessment, visit window discrepancy, or discrepancies from the treatment schedule. Major deviations will be assessed before start of the statistical analyses. Only observed data will be part of the per-protocol analysis. A lesion with missing response at 3-months will be excluded from the calculation of the patient response rate.

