### **Intent-to-treat (ITT) efficacy population:**

This population will consist of the entire population for whom any aspect of treatment with Metvix® cream was initiated. This population will be analyzed using the last observation carried forward (LOCF) method to impute missing values and to avoid possible bias introduced by non-random dropout of patients. A lesion with missing response at 3-months, will be handled as non-complete response in the calculation of the patient response rate.

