### **8.2.2 Efficacy**

The primary endpoint will be lesion response rate determined by clinical assessment (visual inspection and palpation) 3, 12 and 36 months after Metvix® PDT treatment. Lesion response rate is defined as number of lesions in complete response at the follow-up.

The primary hypothesis to be tested will be:

$$H_0: \mu_1 \leq \mu_2 - \delta_0 \text{ vs. } H_A: \mu_1 > \mu_2 - \delta_0$$

Here  $\mu_1$  = expected response rate for treatment regimen 1,  $\mu_2$  = expected response rate for treatment regimen 2,  $\delta_0 = 0.1$ , non-inferiority margin.

As one patient may yield more than one lesion, a mixed effects logistic regression model with patient identity as random factor will be considered. Different lesions within the same patient will be subject to stratified randomization.

A two-sided 95% confidence interval for difference in lesion response rate will be calculated and supplemented by odds ratio from the logistic regression. The calculation of the confidence interval will be based on data pooled across centers.

Efficacy results will be presented for the ITT and for the PP population.

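### Lesions that fail before 36 months have no scheduled cosmetic grade, so the stated analysis rules compare cosmesis mainly among cured lesions or carry forward grades taken before replacement treatment

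*Protocol*

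**What the plan says.** **Status of cosmesis.** Protocol 3.1 reads "The primary endpoint will be lesions cure rate and cosmetic outcome by treatment regime 1", set against the cure rate under regime 2, with assessment at 36 months. The synopsis agrees: "The primary endpoint will be lesions response rate and cosmetic outcome determined by clinical assessment". The statistics section does not. In 8.2.2 the text is "The primary endpoint will be lesion response rate determined by clinical assessment (visual inspection and palpation) 3, 12 and 36 months after" Metvix PDT, with no cosmetic component. Section 8.2.1 defines the primary outcome as binary cure at 3 years, and 8.3 sizes the trial on cure.

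**Who is followed.** The table in 5.6.2 gives the 12- and 36-month visits to "Regime 1/ all lesions in complete response", and words the regime 2 rows in the same way. Section 1.2 withdraws patients who are non-responders at the 3-month control after their latest session, and adds: "They are then offered standard BCC treatment at the discretion of the dermatologist". Section 6.1 and the flow-chart footnote exclude patients with residual tumour on histology. Section 4.4 only encourages withdrawing patients to have the final evaluations, and fixes no 36-month date for them.

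**Missing data.** For the ITT population: "This population will be analyzed using the last observation carried forward (LOCF) method to impute missing values". For the per-protocol population: "Only observed data will be part of the per-protocol analysis". The one explicit failure rule in the ITT paragraph concerns a missing 3-month response, not a cosmetic grade.

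**The concern.** Whether a lesion has a 36-month cosmetic grade depends largely on whether it was cured, and cure is what the regimes may differ on. A regime that fails more of its difficult lesions removes them from its own cosmetic denominator and can look cosmetically better because it cured less.

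Carrying grades forward does not repair this. The scale in 3.1 describes fibrosis, atrophy and pigment change and does not mention residual tumour. A lesion graded well, then found to have failed and treated by other means, can stay in the ITT table as a good 36-month result for its randomised regime. A cosmetic advantage claimed for the simplified regime could then be partly a product of selection. This concerns the cosmetic comparison only.

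**Working it through.** **Inputs.** Planned reference cure at 3 years is 85% (8.3) or 80% (synopsis and 8.2.1). The limit for regime 1 is 75% (8.3) or 70% (synopsis). Recruitment is 187 lesions per group, which is 170 × 1.1 (8.3). The protocol gives no figure for missing cosmetic grades, so there is none to reproduce.

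**Step 1: ceiling on ungraded lesions.** Failures = 187 × (1 − cure rate).

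| Cure rate | Failing | Lesions of 187 |
|---|---|---|
| 85% (planned, 8.3) | 15% | 28.1 |
| 80% (planned, synopsis) | 20% | 37.4 |
| 75% (regime 1 limit, 8.3) | 25% | 46.8 |
| 70% (regime 1 limit, synopsis) | 30% | 56.1 |

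These are cumulative 3-year failures. A failure first seen at the 36-month visit can be graded there, so ungraded share = (1 − cure rate) × share of failures found earlier. The documents give no such share. Assuming 50–100%:

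- planned rates: 0.15 × 0.5 = 7.5% up to 0.20 × 1 = 20%;
- regime 1 at its limit: 0.25 × 0.5 = 12.5% up to 0.30 × 1 = 30%.

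Ordinary loss to follow-up, for which the plan allows 17/187 = 9.1%, comes on top. Exclusion is also written per patient, with 374/277 = 1.35 lesions per patient (4.1), so one failure could cost a cured lesion in the same patient its grade. I have not put a number on that.

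**Step 2: how far the missing grades could move the comparison.** Assume 80% of graded lesions are good or excellent in both arms. The extremes set every ungraded lesion to all good or all bad, in opposite directions by arm.

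- 15% ungraded in each arm: low = 0.80 × 0.85 − (0.80 × 0.85 + 0.15) = −15 points; high = +15 points.
- 25% ungraded in regime 1, 15% in regime 2: low = 0.60 − (0.68 + 0.15) = −23 points; high = (0.60 + 0.25) − 0.68 = +17 points.

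**Step 3: illustration of selection (assumed inputs).** Let 75% of lesions be cured under either regime, with 90% good or excellent cosmesis. Let a further 10% be cured only under regime 2, with 60% good or excellent.

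- Cured only: regime 1 = 90.0%; regime 2 = (0.75 × 0.90 + 0.10 × 0.60)/0.85 = 0.735/0.85 = 86.5%. Regime 1 leads by 3.5 points.
- Standard error, ignoring clustering: √[0.9 × 0.1/(187 × 0.75) + 0.865 × 0.135/(187 × 0.85)] = 3.7 points.
- All lesions, cured with good or excellent cosmesis: regime 1 = 0.75 × 0.90 = 67.5%; regime 2 = 73.5%. Regime 2 leads by 6 points.
- With 40% to 70% instead of 60% in the extra group, regime 1's cured-only lead is 5.9 to 2.4 points.

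The direction reverses, but the cured-only distortion is about one standard error.

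**The case against.** Several stronger readings are tempting, and the documents do not support them.

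- **That 15–25% of lesions in each arm lack a 36-month grade.** 15% follows from the planned rate in 8.3, but 25% is regime 1's non-inferiority limit, not an expected rate in either arm. Both are ceilings.
- **That a failed lesion cannot be graded at 36 months.** It can if the failure is first seen at that visit, and 4.4 leaves an optional final evaluation for those who withdraw.
- **That carry-forward always uses a grade from before failure.** Section 8.1 and the flow chart place cosmesis at the follow-up visits from 3 months, so the last grade may come from the visit where failure was found. Under 3.1, which names only 12 and 36 months, a 3-month failure may have no grade to carry. What the text supports is a grade from before replacement treatment.
- **That cosmesis is settled as primary.** Sections 8.2.1, 8.2.2 and 8.3 speak against it.

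It can also be argued that the missing-data rules were written for response. Section 8.1 names efficacy and cosmetic evaluation separately, 8.2.2 deals with response alone, and cosmetic scoring could be left to an analysis plan that is not shown. That has some force: applying the rules to cosmesis is a reading. But they are the only rules given, they are attached to the efficacy populations, and 3.1 and the synopsis put cosmesis in the primary endpoint. Followed literally, they give the two results described.

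The illustration needs a full 10-point cure deficit, which the cure analysis should normally reveal, and the 6-point reversal comes from that deficit. With equal cure and similar failing lesions in both arms, differential selection largely disappears. Cosmesis among cured lesions is a legitimate description if labelled as such. These points limit the size of the problem but do not remove it.

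**Conclusion.** The point holds in a limited form. The protocol is inconsistent on whether cosmesis is primary. Lesions failing before the 36-month visit have no scheduled grade: at most 15–20% per arm at the planned cure rates, and up to 25–30% in regime 1 at its limit. The true share depends on how many failures are found before 36 months, which the documents do not say. Under the stated rules, the per-protocol comparison is restricted largely to cured lesions and the ITT comparison can carry a grade past failure and other treatment. The distortion is real in direction but modest under the illustrated assumptions, and it does not touch the scoring of cure. It should be corrected before any between-regime cosmetic claim is made.

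**What to change.** In 3.1, the synopsis and 8.2:

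1. State once whether cosmetic outcome is primary or secondary.
2. Exclude cosmetic grades from carry-forward once a lesion has failed.
3. Label the four-point grade among cured lesions as descriptive and conditional on cure, shown beside the number of failed and ungraded lesions in each arm.
4. For any between-regime cosmetic claim, add the proportion cured with excellent or good cosmesis at 36 months over all randomised lesions. Count failure as not achieved, and handle lesions lost without failure as in the cure analysis.

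The cost is wording and one extra table, with no new visits or data. The composite in item 4 is one choice among several. Its downside is that it mixes cosmesis with cure, so a difference in it may simply repeat the cure result. It must therefore stand beside the cured-only description and not replace it.

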## 4. Patient and lesion selection

### 4.1 Number of lesions

277 patients with 374 lesions will be included.

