## **5.2 Randomisation and Emergency Code**

Lesions will be randomized to treatment regime 1 or 2 after treatment by light. In case of multiple BCC, the investigator will number the lesions. The first lesion will be randomized and the next lesion will get the other regime, implying that every second lesion is randomized. The coordinating investigator will supply the randomization code. This is an open study and no emergency code will be required.

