### **8.2.1 Disposition of Lesions**

The number of lesions which are included into the study, which receive Metvix® cream, which are included in safety and/or efficacy evaluation, and which complete each phase of the study, as well as withdrawals will be summarized using counts and percentages of lesions.

Each lesion will be identified, randomized, treated and followed up individually. Patient identification will be recorded anonymously, to account for potential individual susceptibility with respect to response.

The primary outcome is defined as “cure” or “no cure” of a lesion at 3 years, i.e. a binary variable. From previous experience it is expected that the reference treatment leads to a probability of cure of 80 %.

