| AE                  |     |   | X  | X III  |    |    |  |
| Cosmesis            |     |   | X  | X III  | X  | X  |  |
| Biopsy              |     |   | X* | X* III | X* | X* |  |

I: Approved PDT regime with two PDT treatments one week apart

II: New PDT regime with one PDT treatment

III: New PDT regime with one PDT treatment pluss one extra PDT treatment due to non-complete response after 3- month assessment.

\*Clinically suspected recurrences will be examined by histology. Patients with histologically remaining BCC will be excluded from the study.

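### The strict recurrence rate divides patients by lesions and leaves recurrences found before 36 months out of its denominator

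*Protocol*

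**What the plan says.** Section 3.1 of the Protocol sets two recurrence rates under the secondary endpoint. The raw rate is "total number of recurrences divided by the total number of tumours treated". The strict rate is "total number of patients with recurrence divided by number of lesions observed for at least 36 month".

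Other sections fix the unit and the follow-up:

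- Section 8.2.1 makes the lesion the unit: "Each lesion will be identified, randomized, treated and followed up individually".
- Section 4.1 gives the numbers: "277 patients with 374 lesions will be included".
- Section 5.2 allocates within a patient by alternation: "The first lesion will be randomized and the next lesion will get the other regime".
- The follow-up table in section 5.6.2 limits the 12- and 36-month visits to cleared lesions. Its row label for regime 2 is "Regime 2/ all lesions in complete response", and regime 1 has the same rule.
- The biopsy footnote to Table 1 in the Appendix adds: "Patients with histologically remaining BCC will be excluded from the study". Section 6.1 says the same.
- Section 1.2 says that patients with non-complete response "at the control visit 3 months after the latest treatment session are withdrawn from the study".

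The Protocol does not define recurrence.

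**The concern.** The strict rate has two separate faults.

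**Units.** Patients over lesions is not a proportion. A patient with two recurrent lesions adds one to the numerator and up to two to the denominator. Because lesions within a patient alternate between regimes, a patient with a recurrence under each regime counts once in each regime's numerator but only once in the pooled one, so the regime tables do not add up to the total. The same happens across subtype, thickness or marker groups when one patient has tumours of different kinds.

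**Mismatched sets.** The denominator requires 36 months of observation and the numerator does not. A lesion with confirmed recurrence at 12 months is no longer in complete response, so it has no scheduled 36-month visit. Its patient is counted above the line while the lesion is missing below it.

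The secondary objective relates recurrence to thickness, histological subtype and immunohistochemical markers. Groups that differ in how early lesions recur, or in lesions per patient, would show different strict rates even if the same share of their lesions recurred.

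**Working it through.** The Protocol gives no recurrence figure, so there is nothing to reproduce. The check applies the definition as written to assumed counts.

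**Notation.** M = cleared lesions that either recurred by 36 months or were observed that long. R = lesions among M that recurred. E = those of R found before the 36-month visit. P = patients who carry the R lesions.

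- Consistent lesion-level rate: R / M
- Rate as written: P / (M − E)
- Ratio of the second to the first: (P/R) / (1 − E/M)

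P/R is at most 1 and pulls the rate down. The divisor 1 − E/M is also at most 1 and pushes it up. They cancel only when P/R = 1 − E/M.

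**Illustration 1.** The 187 lesions per group come from section 8.3. Everything else is assumed: 9 never clear, 16 are lost, 18 recur, 9 of these by month 12.

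- M = 187 − 9 − 16 = 162; M − E = 162 − 9 = 153
- Consistent rate: 18/162 = 11.1%
- As written, 18 patients: 18/153 = 11.8%
- As written, 17 patients: 17/153 = 11.1%, where the two errors happen to cancel
- As written, 15 patients: 15/153 = 9.8%

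**Illustration 2, with more and earlier recurrence.** Section 8.3 gives 187 recruited against 170 required, so 17 lost. Assumed: 10 never clear, 30 recur, 20 of these at 12 months.

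- M = 187 − 10 − 17 = 160; M − E = 160 − 20 = 140
- Consistent rate: 30/160 = 18.8%
- As written, 30 patients: 30/140 = 21.4%
- As written, 22 patients (30 × 277/374 = 22.2): 22/140 = 15.7%

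**Range.** Let r be the recurrence risk among cleared lesions (assumed 10–20%) and e the share of recurrences found before 36 months (assumed 50–75%). With one recurrent lesion per patient, the rate as written is r/(1 − re).

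- Low end: 0.10/(1 − 0.05) = 10.5%
- High end: 0.20/(1 − 0.15) = 23.5%
- Multiplied by 277/374 = 0.741: 7.8% and 17.4%

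So a true 10–20% is reported as 10.5–23.5% or as 7.8–17.4%, depending only on how recurrences cluster in patients. The ratio 277/374 describes all planned lesions, not recurrent ones, and serves only as a rough guide to clustering.

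**Exclusion by patient.** These sums remove only the recurrent lesion. The Table 1 footnote excludes the patient. If that is applied literally, the patient's other cleared lesions also fall short of 36 months and the denominator shrinks further.

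**The case against.** The strongest reply is that the effect is small and partly contrived. In the first illustration the denominator fault moves the rate by 0.7 points (11.8% against 11.1%). Within one regime, clustering is limited: with alternating allocation, two lesions under the same regime normally need at least three lesions in one patient, and the planned mean is 374/277 = 1.35. Fifteen patients for 18 recurrent lesions in one arm is therefore a generous case. This stands. By regime, the upward error will usually dominate. Clustering matters more in subtype, thickness and marker groups pooled over regimes.

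Section 3.1 also promises lesion recurrences by regime at 12 and 36 months, so lesion-level data will exist. That makes the correction easy, but it does not make the stated definition right. Nor can this be left to a SAP: the Protocol states the formula, and a SAP that followed it would carry the error over. One could read the 36-month condition loosely, as outcome known through 36 months, but the wording does not say that.

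A reader might go further and infer that the raw rate is wrong too because it treats never-cleared lesions as free of recurrence. The Protocol does not support this. Recurrences over treated tumours is a valid crude proportion and is labelled raw. Whether never-cleared lesions count as recurrences is open: the synopsis uses lesion recurrence at 3 years as the binary outcome where section 8.2.1 has cure or no cure, and the Table 1 footnote speaks of suspected recurrences for a biopsy row that includes the 3-month visits. What is firm is the missing definition. In the second illustration the raw rate is 30/187 = 16.0% or (30 + 10)/187 = 21.4%, depending on the reading.

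Nor does the raw denominator by itself rank a worse regime as better. Take two assumed groups of 187: 37 never clear and 15 of 150 recur in one; 9 never clear and 18 of 178 recur in the other. The raw rates are 15/187 = 8.0% and 18/187 = 9.6%, while cure (ignoring losses) is 135/187 = 72% and 160/187 = 86%. Restricting to cleared lesions gives 15/150 = 10.0% and 18/178 = 10.1%, which still does not show the first group as worse. Any rate of recurrence after clearance omits primary failures; the cure outcome captures them.

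**Conclusion.** The strict rate is wrong as written. The unit mismatch is certain from the wording. The missing early recurrences follow from the plain wording together with the follow-up table and the exclusion rule. The net direction cannot be known in advance. In the illustrations the error runs from about 3 points too low (15.7% against 18.8%) to about 3 points too high (21.4% against 18.8%), and it can be close to nil. Those sizes rest on assumed clearance, recurrence, timing and clustering; only the lesion and patient totals and the group sizes come from the Protocol.

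The point is limited to one secondary descriptive measure. It does not show that the raw rate is invalid, and it does not touch the primary cure/no-cure outcome or its non-inferiority test.

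**What to change.** In section 3.1, replace the strict definition along these lines: the number of lesions with histologically confirmed recurrence by 36 months, divided by the number of lesions that reached complete response and then either recurred by 36 months or were followed without recurrence for at least 36 months.

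Add that recurrence means return of tumour after documented complete response. Report never-cleared lesions as a separate count beside the raw rate, which may stay as a crude share of treated tumours. Because the corrected strict rate still leaves out lesions lost without recurrence, give their number next to it.

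The cost is a few sentences. Lesions are already numbered in the CRF and followed individually, so no new data, visits or sample size are needed. Whether to add a time-to-recurrence estimate is a choice for the SAP and is not part of this correction.
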